**Fig. 3 Fig3:**
[figure not shown]
Schedule of events. Study assessments will be performed over 45 days for each cohort. The schedule lists all the interventions, tests, and pre- and post-test assessments that will be performed at screening (days − 28 to − 3), cardiopulmonary exercise testing (CPET) at baseline (day 1), treatment (days 8 and 15), and safety follow-up (day 45) visits. Adverse event assessments and interval history reviews will be conducted at each visit. *6MWT* 6-minute walking test, *6MWD* 6-minute walking distance, *BP* blood pressure, *DASI* Duke Activity Status Index, *ECG* electrocardiogram, *HR* heart rate, *HRR* heart rate recovery, *NYHA* New York Heart Association, *O*_*2*_ oxygen, *PAH* pulmonary arterial hypertension, *PFT* pulmonary function testing, *PGI-S* Patient Global Impression of Severity, *PK* pharmacokinetic, *RPE* rating of perceived exertion, *SPO*_*2*_ peripheral oxygen saturation, *WHO* World Health Organization. *Potential patients will be screened approximately 3 days (≤ 28 days) before baseline CPET visit 2. ^†^Patients will be scheduled for treatment CPET visit 3, approximately 7 days after the baseline CPET visit 2. ^‡^If a patient prematurely discontinues the study any time before dosing or treatment CPET visit 3 because of an adverse event or patient safety concern, the patient should return to the clinic as soon as possible for an early termination study visit. ^§^Medical history will include a detailed PAH disease-specific medical history. ^II^Clinical laboratory tests may be repeated at the baseline CPET visit 2 if screening laboratory results are deemed clinically significant and warrant repeat testing. Clinical laboratory includes hematology, chemistry, and urinalysis. Prothrombin time international normalized ratio will also be tested in patients taking oral vitamin K antagonists. ^¶^Urine or serum pregnancy test at screening visit 1 required and a urine or serum pregnancy test at visit 3 and visit 4. **Either a single 0.5-mg dose (cohort 1) or a single 1.0-mg dose (cohort 2) of RT234 will be administered 30 minutes before CPET at visit 3 and 30 minutes before the 6MWT at visit 4. ^††^Interval history will include any signs, symptoms, or events experienced by the patient since the previous study visit. ^‡‡^Physical examinations at screening will be complete; all other physical examinations will be symptom directed. ^§§^Height will be obtained only at screening visit 1. ^II II^Resting vital signs (BP, HR, respiration rate, body temperature, and pulse oximetry [SPO_2_]) after resting for 5 minutes (sitting). Vital signs should be taken before any blood draw. BP, HR, and SPO_2_ will also be measured during CPET and into recovery (HR via continuous ECG monitoring during CPET and for 6 minutes post CPET, BP assessment every 2 minutes during CPET and for 6 minutes post CPET, and SPO_2_ assessment every minute during CPET and for 6 minutes post CPET) and at treatment 6MWT visit 4 (before RT234 dosing; 5 and 15 minutes post dose before 6MWT at 30 minutes post dose; and at 60 and 120 minutes post dose). ^¶¶^Continuous ECG monitoring will be collected during CPET and for 6 minutes post CPET. ***PFT may be completed at screening and/or baseline to confirm eligibility if historical PFT results within 6 months before screening are not available. ^†††^During the screening period, two 6MWTs will be performed at least 2 days apart, and the mean of the distance walked will be used for eligibility. If tolerable for the patient, the two 6MWTs at screening can be performed on the same day after a minimum of 2 hours between each test. The two screening 6MWDs must have a relative difference (i.e., [absolute difference between the two 6MWDs] / [mean of the two 6MWDs]) of ≤ 15%. If the difference is > 15%, a third 6MWT will be done during screening. If after the third 6MWT the relative distance is still > 15%, the Sponsor Medical Monitor will be contacted. The two longest 6MWDs will be averaged to determine the baseline 6MWD. ^‡‡‡^ The CPET assessments conducted at Visits 2 (pre dose) and 3 (post dose) will be conducted at approximately the same time of day (within 2 hours). ^§§§^PGI-S before CPET and at 2 minutes cool down off treadmill but still wearing the mask, then at 5-minute intervals: 7, 12, and 17 minutes with the mask off. For the 6MWT, PGI-S will be taken before and at 2 minutes after completion of the test. ^II II II^Modified Borg Dyspnea Scale assessment every minute during CPET and for 6 minutes post CPET. ^¶¶¶^Borg RPE Scale assessment every 2 minutes during CPET and for 6 minutes post CPET. ****Angina Scale assessment every 2 minutes during CPET and for either 6 minutes post CPET or, if indicated, until symptom recovery. ^††††^DASI assessment 10 minutes post CPET. ^‡‡‡‡^PK samples will be collected at visits 3 and 4 before RT234 dosing; at 3, 15, and 30 minutes post dose; immediately at the end of the exercise period; and at 45, 75, 120, 180, and 240 minutes post dose

The assessment of safety will involve evaluating the adverse event profile and acute physical and cardiac symptoms of single doses (0.5 or 1.0 mg) of RT234. The incidence and severity of TEAEs will be summarized by Medical Dictionary for Regulatory Activities (current version) System Organ Class and Preferred Term, National Cancer Institute Common Terminology Criteria for Adverse Events (current version) grade, and causality (attribution to study treatment and related/not related to investigational medicinal product). Changes in vital signs (blood pressure [BP], heart rate, respiratory rate, body temperature, and pulse oximetry) will be monitored, and physical examinations and 12-lead electrocardiograms (ECGs) will be conducted to measure the change from baseline to post dose.

Exploratory endpoints include the proportion of patients with improvement in risk category (low, intermediate, or high) for the VE/VCO_2_ slope criteria (defined in the 2015 European Society of Cardiology/European Respiratory Society Guidelines for the Diagnosis and Treatment of Pulmonary Hypertension [1]) during CPET from baseline to post dose, and changes in the following additional CPET parameters from baseline to post dose, according to the recommendations of the American Heart Association [16]: ECG response to exercise, VO_2_ at ventilatory threshold, change in respiratory exchange ratio at peak VO_2_, systolic BP response to exercise, pulse oximetry response to exercise, the non-peak Modified Borg Dyspnea Scale Score [15] throughout exercise (at every non-peak minute during CPET and for 6 minutes post CPET), the Borg Rating of Perceived Exertion Scale [17] throughout exercise (every 2 minutes during CPET and recovery), the Duke Activity Status Index [18] and the 4-Point Angina Scale [19].

The PK parameters of vardenafil and the relationship between vardenafil exposure and changes in CPET parameters and 6MWD will also be determined. Plasma samples will be collected at visits 3 and 4 before RT234 dosing; at 3, 15, and 30 minutes post dose; immediately at the end of the exercise period; and at 45, 75, 120, 180, and 240 minutes post dose. Vardenafil concentrations will be measured in the PK samples as described previously [13]. Estimators of PK parameters will include T_max_, C_max_, area under the curve from time 0 to the last measurable concentration (AUC_0–Last_), AUC from time 0 to infinity (AUC_0–Inf_), and half-life (t_1/2_). For CPET, exposure–response analysis will be based on AUC_0–Last_ and change from baseline in peak VO_2_ measured during CPET 30 minutes after RT234 dosing; for the 6MWT, exposure–response analysis will be based on AUC_0–Last_ and change from baseline 6MWD (mean of the screening 6MWDs) to the 6MWD 30 minutes after RT234 dosing.

### Statistical analysis

The estimated total sample size is 86 enrolled patients, with a 5% dropout rate and a computed sample size of 17 and 26 patients with up to two and three background medications, respectively, per dose cohort (0.5 and 1.0 mg). This was derived using a one-sample two-sided *t* test (0.05 significance level and 80% power) to test the null hypothesis of no change in peak VO_2_ from baseline to post dose assessed during CPET performed 30 minutes after RT234 dosing. The assumed mean change from baseline is 1.5 and 1.2 mL O_2_·kg^–1^·min^–1^ [20] for patients with up to two and three background medications, respectively, in each dose cohort. A standard deviation of 2 mL O_2_·kg^–1^·min^–‍1^ is assumed for each dose cohort and background medication group.

The primary efficacy analysis will be conducted on the modified intention-to-treat (mITT) analysis set, which comprises all treated patients with baseline and post-baseline assessment of peak VO_2_. This mITT analysis set will serve as the basis for all efficacy analyses. The analysis procedure will be repeated for the per-protocol analysis set (all mITT patients who do not experience any major protocol violations) using a one-sample *t* test (if peak VO_2_ follows a normal distribution) to test the two-sided null hypothesis (0.05 significance level) of no change in peak VO_2_. The 95% CI for peak VO_2_ mean change will be derived from the *t* test if the normality assumption is not rejected. If it is rejected, a one-sample Wilcoxon signed-rank test will be used to determine the median change in peak VO_2_ with a 95% CI estimate.

The secondary efficacy analyses will be conducted on the mITT analysis set and will be repeated with the per-protocol analysis set, as described for the primary efficacy analyses. Because this study is exploratory (open-label, uncontrolled, and non-randomized) and its focus is on dose-escalation safety and activity, formal inferential statistics are not planned, and multiplicity adjustment will not be performed.

Safety data will be summarized descriptively for the safety analysis set (all patients who receive at least one dose [partial or complete] of RT234; safety parameters will be summarized for the pooled background medication groups in each dose cohort) on the basis of TEAEs, clinical laboratory assessments, vital signs, weight, and physical examinations. Changes from baseline in these assessments will be summarized by cohort using standard descriptive statistics. TEAE incidence rates will be summarized by frequency and percentage for each cohort and overall.

Planned PK parameters (T_max_, C_max_, AUC_0–Last_, AUC_0–Inf_, and t_1/2_) will be calculated for treated patients with available PK measurements using the standard linear trapezoidal convention for all available drug concentration measurements. Standard descriptive statistics (mean, median, n, standard deviation, minimum, maximum, and coefficient of variation) will be used to summarize the PK parameters, along with the 90% CI, when appropriate.

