### Treatment protocol

Once patient eligibility has been confirmed, the study will begin with the screening visit(s) (visit 1), which will occur between 28 and 3 days before the CPET baseline visit (Fig. 2). The screening visit(s) will include two 6MWTs performed at least 2 days apart or, if tolerable to the patient, at least 2 hours apart on the same day (this will account for the learning effect associated with the 6MWT [14]; the relative difference between the two measurements must be ≤ 15%). The two screening 6MWDs will be averaged to determine the baseline 6MWD. At the CPET baseline visit (visit 2; day 1), enrolled patients will return to the testing center for pre-test assessments, CPET, and post-test assessments (Fig. 3). Eligible patients whose baseline CPETs are deemed evaluable by the CPET Core Laboratory will enter the treatment period (visits 3 and 4) for dosing with RT234 and post-dose CPET and 6MWT. At the CPET treatment visit (visit 3; day 8), patients will return to the testing facility for pre-CPET assessments and a single dose of RT234 (0.5 mg for cohort 1 and 1.0 mg for cohort 2), which will be administered with the aid of the study team. CPET will be performed 30 minutes post dose, at approximately the same time of day at each visit (within 2 hours), followed by post-test assessments. At the 6MWT treatment visit (visit 4; day 15), patients will undergo pre-6MWT assessments and receive a single dose of RT234. Patients will perform a 6MWT 30 minutes post dose and will then undergo post-test assessments. Plasma samples for PK analyses will be collected before and after RT234 dosing at visits 3 and 4. RT234 will only be administered to patients during visits 3 and 4 (Fig. 1); patients will not use RT234 outside these two visits. Patients will remain at the clinic for PK sampling and safety monitoring for 4 hours once all tests have been completed during visits 3 and 4, and safety monitoring will continue for 30 days after visit 4. Visit 5 (day 45 ± 3-day window) will involve a follow-up telephone call assessment of safety.

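### The single mITT set requires a post-dose peak VO2, so valid visit 4 walk data can be dropped and some dosed patients leave the primary analysis unreported

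*Protocol article*

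**What the plan says.** In the article's Statistical analysis section, the mITT set "comprises all treated patients with baseline and post-baseline assessment of peak" VO2. The scope of the set follows: "This mITT analysis set will serve as the basis for all efficacy analyses". The rule is repeated for the secondary endpoints: "The secondary efficacy analyses will be conducted on the mITT analysis set and will be repeated with the per-protocol analysis set". The per-protocol set is "all mITT patients who do not experience any major protocol violations", a subset of mITT. No other efficacy set is stated.

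The Treatment protocol section places the two post-dose tests at different visits, each with its own dose:

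- Peak VO2: "At the CPET treatment visit (visit 3; day 8), patients will return to the testing facility for pre-CPET assessments and a single dose of RT234".
- 6MWD: "At the 6MWT treatment visit (visit 4; day 15), patients will undergo pre-6MWT assessments and receive a single dose of RT234". Then: "Patients will perform a 6MWT 30 minutes post dose and will then undergo post-test assessments".

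Under Outcome measures and endpoints, the change in 6MWD runs from the mean of the screening walks to the post-dose walk. The change in PGI-S for the 6MWT runs from screening to post dose.

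**The concern.** Membership of the efficacy set is decided by one test, the visit 3 CPET, yet the set governs endpoints measured at another visit after another dose. This has two consequences.

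1. Walk data that are complete in themselves (screening baseline and visit 4 value) are excluded because a different test, a week earlier, gave no peak VO2.
2. Membership is settled after dosing, because the CPET follows the dose by 30 minutes. A patient who is dosed and cannot start the test, or whose test gives no peak VO2, is not in the primary analysis. If the reason is poor tolerance, the remaining patients have a better mean change than all those dosed. With no control arm, nothing offsets this.

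**Working it through.** **Step 1: which endpoints need the visit 3 CPET.**

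| Endpoint | Baseline | Post-dose value | Needs visit 3 peak VO2? |
|---|---|---|---|
| Peak VO2 | visit 2 CPET | visit 3 CPET | yes |
| 6MWD | screening walks | visit 4 walk | no |
| PGI-S for 6MWT | screening | visit 4 | no |

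**Step 2: can a patient miss the visit 3 value and still walk at visit 4?** The Treatment protocol section admits patients to visits 3 and 4 once the Core Laboratory finds the baseline CPET evaluable. That makes a baseline peak VO2 close to automatic for treated patients, so the post-dose value is the condition that bites. No further condition is stated between visits 3 and 4. A patient with an unusable visit 3 test may therefore return, be dosed and walk. Under the stated rule that walk is not analysed.

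**Step 3: the plan's own sample size.** Inputs from Statistical analysis: one-sample two-sided t test, alpha 0.05, power 80%, SD 2, mean change 1.5 (up to two background medications) or 1.2 (three), dropout 5%. Exact power from the noncentral t distribution, with noncentrality (mean/SD)·√n:

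- Mean 1.5: n = 16, power 80.1%. 16/0.95 = 16.8, rounded up to 17.
- Mean 1.2: n = 24, power 80.4%. 24/0.95 = 25.3, rounded up to 26.
- Total: 2 × (17 + 26) = 86, which reproduces the stated figure.

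The allowance covers 1 loss in 17 and 2 in 26 from all causes. With 3 lost per group, power is 73.7% (n = 14) and 78.5% (n = 23).

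**Step 4: possible effect on the primary mean.** The article gives no rate of dosed patients without a post-dose peak VO2 and no value for their change. Both are assumed here: a missing fraction f of 5%, 10% or 15%, and a true change m of 0 or -2 mL/kg/min in those patients. With mITT mean d,

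all-dosed mean = (1 − f)·d + f·m

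| f | of 86 dosed | d = 1.5, m = 0 | d = 1.5, m = −2 | d = 1.2, m = 0 | d = 1.2, m = −2 |
|---|---|---|---|---|---|
| 5% | about 4 | 1.43 | 1.33 | 1.14 | 1.04 |
| 10% | about 9 | 1.35 | 1.15 | 1.08 | 0.88 |
| 15% | about 13 | 1.28 | 0.98 | 1.02 | 0.72 |

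For example, 0.85 × 1.5 + 0.15 × (−2) = 1.275 − 0.300 = 0.975. The fall is 5% at the mildest corner (0.075/1.5 and 0.06/1.2). At the harshest it is 35% (0.525/1.5) and 40% (0.48/1.2).

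**The case against.** A reader might infer that mITT holds only patients who completed the visit 3 CPET, that the estimate is therefore certainly biased toward the drug, and that the planned 5% dropout gives the size of that bias. The article does not support this, for four reasons.

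- The definition asks for an assessment of peak VO2, not a completed or maximal post-dose test. The respiratory exchange ratio criterion in Table 1 applies to the baseline CPET. A patient who stops early with symptoms can still have a peak VO2, possibly a low one, and stay in the set.
- The 5% is dropout among enrolled patients. Some may leave before any dose (the Fig. 3 legend provides for discontinuation before dosing), and they belong to no treated set. Reading the rounded-up allowances of 1 in 17 and 2 in 26 as the excluded patients would give 6 of 86, which is 7%, not 5%.
- Lost walks and upward bias largely need different patients. The first needs someone well enough to return and walk at visit 4, the second someone too unwell to exercise at visit 3. A technical CPET failure loses a walk without favouring the drug.
- Patients without a peak VO2 remain in the safety set, and the Study design section says that data on discontinuations with an explanation will be summarized and listed. The study is declared exploratory, without formal inference. Missing-data methods commonly sit in a statistical analysis plan that is not shown.

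All of this limits the size and certainty of the bias. It does not answer the point about the walk endpoints: the article itself fixes one peak VO2 set for every efficacy analysis, so this is a stated rule rather than a detail left for later. The listing of discontinuations also does not reach patients who stay in the study without a peak VO2.

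**Conclusion.** The rule is badly fixed for 6MWD and the PGI-S for the 6MWT. It excludes a dosed patient's valid visit 4 data for a reason unrelated to those endpoints, and the per-protocol analysis inherits the exclusion. This follows from the text alone; the number of patients affected is unknown.

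The effect on the primary analysis is conditional. If dosed patients without a visit 3 peak VO2 are missing because of poor tolerance, the mean change may be overstated. The ranges of 1.43 to 0.98 (from 1.5) and 1.14 to 0.72 (from 1.2) rest entirely on the assumed 5% to 15% missing and the assumed change of 0 to -2 mL/kg/min, neither of which the article supplies. They show what could happen and do not estimate what will.

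Severity is minor to moderate. The study is exploratory, the planned N of 86 is unaffected, and the remedy is nearly free. It still deserves correction, because the Discussion says the results will inform the design of phase III trials.

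**What to change.** 1. Define the efficacy set per endpoint: all treated patients with a baseline and a post-dose value of that endpoint, with the per-protocol set nested in it. The article already follows this principle for PK, where the parameters are calculated for treated patients who have PK measurements.
2. Report how many dosed patients have no post-dose peak VO2, by dose cohort and background medication group, with reasons that separate adverse event or inability to exercise from technical failure.
3. Add one sensitivity analysis of the primary endpoint on all dosed patients, for example with zero change for those missing because of an adverse event or inability to exercise. A worse-than-zero value can serve as a stress test. Either value is an assumption and should be labelled so.

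The cost is a wording change, one table and one extra analysis. No visit, procedure or sample size changes. The downside is that the sensitivity estimate is likely to be slightly less favourable than the mITT estimate.

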### Outcome measures and endpoints

The primary efficacy endpoint is the change from baseline in peak oxygen consumption (VO_2_) measured during CPET performed 30 minutes after a single dose of 0.5 mg or 1.0 mg RT234. The secondary efficacy endpoints are change from baseline in 6MWD (mean of two 6MWDs at screening) to the 6MWD measured 30 minutes after RT234 dosing; change from baseline to post dose in the minute VE/VCO_2_ slope during CPET; change from baseline to post dose in the response of the partial pressure of end-tidal carbon dioxide apex to exercise (i.e., highest level during CPET); change from baseline to post dose in the duration of exercise during CPET; change from baseline to post dose in peak perceived dyspnea during CPET, as assessed by the Modified Borg Dyspnea Scale Score [15]; change from baseline to post dose in Patient Global Impression of Severity (PGI-S) for CPET (assessed before CPET and after a 2-minute cooldown after treadmill exercise while wearing mask, and then at 5-minute intervals [7, 12, and 17 minutes] without a mask); and changes from screening to post dose in PGI-S for 6MWT (assessed before the 6MWT and at 2 minutes after completion of the 6MWT).

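### PGI-S falls under the peak VO2 rule with no reading named as the endpoint; a median change can then read zero although clearly more patients improve than worsen

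*Protocol article*

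**What the plan says.** **Endpoint.** In the Protocol article, Outcome measures and endpoints, one secondary efficacy endpoint is the "change from baseline to post dose in Patient Global Impression of Severity (PGI-S) for CPET". It is read before the test and then 2, 7, 12 and 17 minutes afterwards; the footnotes to the schedule of events (Fig. 3) give the same five times. A second PGI-S endpoint belongs to the walking test, "assessed before the 6MWT and at 2 minutes after completion of the 6MWT". Neither place says which reading, or which summary of the readings, is the endpoint value.

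**Method.** In Statistical analysis, the primary rule is a one-sample t test if the data look normal, otherwise a one-sample Wilcoxon signed-rank test with a median change and 95% CI. The secondary analyses use the mITT set and "will be repeated with the per-protocol analysis set, as described for the primary efficacy analyses". PGI-S is not excepted and no other method for secondary endpoints appears. The same section describes the study as exploratory, with no formal inference planned and no adjustment for multiplicity.

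**Comparable measures.** For Borg dyspnea, the peak score is the secondary endpoint and the non-peak scores are exploratory. For the three-level VE/VCO2 risk category, the exploratory endpoint is the proportion of patients who improve.

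**The concern.** A change on a scale with a few ordered levels takes only a few values, many of them zero. Such data will almost always fail a normality test, so the reported result becomes a median. A median of such scores says little about how many patients improved against how many worsened: it stays at zero until half of them have moved in one direction.

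For the CPET, one endpoint name covers five readings, so the result to be headlined is not fixed in advance. PGI-S and peak Borg dyspnea are the only patient-reported symptom measures among the secondary endpoints. The Discussion presents the product as relief for exertional symptoms and says the results will inform phase III design, so a readable symptom estimate is worth having.

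**Working it through.** **1. Group sizes.** Inputs from Statistical analysis: "0.05 significance level and 80% power", two-sided one-sample t test. "The assumed mean change from baseline is 1.5 and 1.2" mL/kg/min. "A standard deviation of 2 mL" per kg per minute in every group, "with a 5% dropout rate". The exact noncentral t calculation gives:
- 1.5/2 = 0.75: n = 16, power 80.1%; 16/0.95 = 16.8, rounded up to 17.
- 1.2/2 = 0.60: n = 24, power 80.4%; 24/0.95 = 25.3, rounded up to 26.
- Total 2 × (17 + 26) = 86.

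This reproduces the stated "computed sample size of 17 and 26 patients with up to two and three background medications, respectively, per dose cohort", with dropout already included. I use n = 17, n = 26, and 17 + 26 = 43 for a whole dose cohort.

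**2. Assumptions.** The article gives neither the number of PGI-S levels nor any response rate. I assume a change of −1 (improved), 0 or +1 (worse), 10% worsening, and 30% to 60% improving.

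**3. When the sample median is zero.** It is zero when fewer than half improve and fewer than half worsen. With 10% worsening the second condition is practically always met, so P(median = 0) ≈ P(X ≤ m), where X is binomial(n, share improving) and m = 8, 12 and 21 for n = 17, 26 and 43. The Hodges-Lehmann estimate (the median of pairwise averages, usually paired with the signed-rank test) and the signed-rank rejection rate (tie-corrected, two-sided 5%) come from 4,000 simulated samples per case.

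| Improve / same / worse (%) | Sample median = 0, n = 17 / 26 / 43 | Hodges-Lehmann = 0 | Signed-rank rejects |
|---|---|---|---|
| 30 / 60 / 10 | 96 / 97 / >99% | 68 / 70 / 72% | 24 / 35 / 58% |
| 35 / 55 / 10 | 90 / 92 / 98% | 53 / 51 / 50% | 33 / 48 / 72% |
| 40 / 50 / 10 | 80 / 80 / 91% | 39 / 35 / 29% | 40 / 59 / 85% |
| 45 / 45 / 10 | 66 / 63 / 75% | 27 / 21 / 14% | 50 / 71 / 92% |
| 50 / 40 / 10 | 50 / 42 / 50% | 18 / 12 / 5% | 59 / 80 / 96% |
| 60 / 30 / 10 | 20 / 11 / 9% | 7 / 3 / 1% | 74 / 93 / 99% |

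Shapiro-Wilk rejected normality in essentially every three-level sample. With changes from −2 to +2 it rejected in 83% to 100%, and with 40% improving and 15% worsening the sample median was zero in 80 / 80 / 91%.

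**4. Two worked cases.** The net proportion is (b − c)/n, with b improved and c worse; its standard error is √[(b + c) − (b − c)²/n]/n.
- n = 17: 8 improve, 8 unchanged, 1 worse. The 9th ordered value is 0, so the median is 0. Sign test p = 2 × (1 + 9)/2⁹ = 0.039. Hodges-Lehmann −0.5. Net 7/17 = 41%; SE = √(9 − 49/17)/17 = 0.145; 95% CI 13% to 70%.
- n = 26: 12 improve, 12 unchanged, 2 worse. The 13th and 14th values are both 0, so the median is 0. Sign test p = 2 × (1 + 14 + 91)/2¹⁴ = 0.013. Hodges-Lehmann −0.5. Net 10/26 = 38%; SE = √(14 − 100/26)/26 = 0.123; 95% CI 14% to 62%. One more improver (13 of 26) moves the median to −0.5.

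**5. Which test to keep.** With changes of −2, −1, 0 and +1 (5% at −2, 10% worsening), at n = 16 and 24, the signed-rank test rejected in 31% and 47% of samples with 35% improving, and in 48% and 71% with 45% improving. The exact sign test rejected in 19% and 34%, and in 34% and 59%.

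**The case against.** **The cross-reference is ambiguous.** The phrase pointing back to the primary analyses could cover only the analysis sets, and every sentence on the t test, normality and Wilcoxon test names peak VO2. That is a possible reading. On it, however, the article gives no method at all for the secondary endpoints, and nothing sets PGI-S apart.

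**It is detail for the SAP.** How an ordinal scale is tabulated is often settled there, and nothing here rules out a shift table. This lowers the priority. What remains is that the article does state a method and an endpoint that fit each other poorly, while it picks one reading for Borg dyspnea and a proportion improved for the risk category.

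**Stronger readings.** A reader might infer three things that the article does not support:
- *The PGI-S median will usually be zero.* This depends on assumed rates and on the estimator. At 50% improving it is about a coin toss; at 60% it is the exception. With the Hodges-Lehmann estimate, zero is the minority result from 40% improving upward. The article does not say which median estimate it means.
- *The method cannot show an effect.* The signed-rank test uses direction and size of change, and does detect the shift.
- *Five readings will produce false claims of efficacy.* The article openly disclaims formal inference and multiplicity control, and does not say that PGI-S will be tested at every reading in every dose and background-medication group. The gap is that no reading is named, not an undisclosed error rate.

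**Conclusion.** The point holds in a limited form. If the stated rule is applied to PGI-S, the median branch will nearly always be used, and the sample median can read zero when clearly more patients improve than worsen, provided fewer than about half improve. At 35% to 45% improving and 10% worsening this happens in about 63% to 92% of groups of 17 or 26; at 60% improving, in 11% to 20%. These figures rest on assumed response rates and scale levels, and on the sample median being the value reported. The loss is in the estimate, not the test.

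Independently of those assumptions, the endpoint value among the five CPET readings is not defined. Both matters concern secondary endpoints of an exploratory study. The priority is minor.

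**What to change.** - Name one post-exercise reading in advance as the PGI-S endpoint and show the others as supportive. Two minutes is the only post-exercise time common to the CPET and the 6MWT. For the CPET it is taken during cooldown with the mask on, so the sponsor may prefer another reading; what matters is that one is fixed beforehand.
- In place of the median change, report the numbers improved, unchanged and worse in a shift table, with the net proportion improved and its 95% CI.
- If a p value is wanted, keep the signed-rank test; the exact sign test was less powerful in the check above.

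The cost is a few lines of analysis text, with no new data. The downside is that the net proportion ignores how far a patient moved; the shift table shows that.
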